## **7.2 PROPOSED ANALYSES**

Characteristics of participants will be compared informally between treatment arms at baseline. The main analysis of the primary outcome will be intention-to-treat. Cox proportional hazards models will be used to estimate the hazard ratio of the rate of late stage lung cancer in the intervention arm compared to the control arm.

Participants who are lost to follow up will be censored. The models will adjust for age, gender smoking history and practice. If appropriate, random cluster effects will be included rather than fixed effects for practices. A similar methodology will be used for the secondary outcomes of comparisons of mortality rates (secondary outcomes 3a and 3b). A subsequent analysis will compare the outcomes of those with EarlyCDT positive in comparison to those in the intervention group with EarlyCDT negative (primary contrast for this analysis) and those in the control group (secondary analysis 1). Comparisons of proportions (secondary analyses 1 and 4) will be carried out using chi square tests. Fishers exact test will be used if the numbers of events are small.

The analyses of the questionnaire responses (secondary analysis 5) will be carried out using the appropriate 2 sample t tests and regression methods at baseline. Non parametric tests will be used if there is evidence of non-normal scores. Multilevel models will be used to analyse the repeated scores during follow up.

Poisson regression models, adjusting for follow up time if necessary, will be used to investigate the other clinical measures (secondary outcomes 6 and 7).

### **7.2.1 Cost effective analysis**

The short-term within-trial analysis will compare the costs and outcomes associated with the intervention group to those of the comparison group at 24 months. A longer term analysis will employ a decision analytic model to link the short term outcomes measured within the trial to potential longer term impacts on health (for example in

terms of impacts on the development of cardiovascular disease, diabetes etc.). Both analyses will utilise the NHS and personal social service perspective favoured by NICE.

### **7.3 MISSING DATA**

The extent of missing data will be examined and, if necessary, methods such as multiple imputation will be implemented to provide robust results, assuming data are missing at random (MAR).

### **7.4 TRANSFER OF DATA**

Transfer of Data will be achieved according to standard TCTU SOPs (Study Operations Manual).

### **7.5 PREGNANCY**

The female age group in this study (50 to 75 years) are unlikely to be pregnant. However, assessment of risk is established when all women are asked about the possibility of pregnancy prior to any imaging investigations as per usual NHS risk assessment protocols.

## **8 TRIAL MANAGEMENT AND OVERSIGHT ARRANGEMENTS**

### **8.1 TRIAL MANAGEMENT GROUP**

The trial will be overseen by a Trial Steering Committee (TSC) and a Trial Management Committee (TMC) consisting of the CI and co-investigators, trial managers and with representation for research nurses and SPCRn. Day-to-day management of delivery of the trial will be achieved through the Trial Operations Group chaired by the Assistant Director of TCTU and comprising project and trial managers, data managers, statistician and software developers.

## **8.2 TRIAL MANAGEMENT**

The Senior Trial Manager and Trial Manager will oversee the study and will be accountable to the CI. The Senior Trial Manager will be responsible for other trial processes hosted within the TCTU. However, this remains the overall responsibility of the CI. Any queries will be resolved by the CI or delegated member of the trial team.

A study-specific Delegation Log will be prepared for each site, detailing the responsibilities of each member of staff working on the trial.

## **8.3 TRIAL STEERING COMMITTEE**

The TSC will be a mixture of lung cancer investigators and independent members. The TSC will be chaired by an independent, senior clinician with expertise in cancer research and clinical trials. Other independent members will include a statistician and a senior trial manager and a trial methodologist. The TSC will also have two patient representatives. The TSC will meet annually, with the first meeting being shortly after the start of the project. The terms of reference of the TSC and the draft template for reporting are detailed in Appendix 2. .

## **8.4 DATA MONITORING COMMITTEE**

The DMEC will comprise of three independent members plus an independent statistician. The Chair will be a senior clinician or statistician with experience of clinical trials and DMECs. The two other independent members will be a senior trial manager or methodologist, together with a second clinical expert. The DMEC will meet annually in the first instance although the chair will be free to increase the frequency of meetings as required. The first DMEC will be held shortly after the first TSC.

The terms of reference of the DMEC are detailed in Appendix 3.

## **8.5 INSPECTION OF RECORDS**

The CI, PIs and all institutions involved in the study will permit trial related monitoring, audits, REC review, and regulatory inspection(s). In the event of an audit, the CI agrees to allow the Sponsor, representatives of the Sponsor or regulatory authorities direct access to all study records and source documentation.

## **8.6 RISK ASSESSMENT**

A pre-Sponsorship study risk assessment was carried out by the TASC Research Governance Manager prior to Sponsorship approval being granted.

## **8.7 STUDY MONITORING**

The Sponsor will determine the appropriate extent and nature of monitoring for the study and will appoint appropriately qualified and trained monitors.

### **8.7.1 Potential Risks**

#### **8.7.2 Blood sampling**

Veins and arteries vary in size from one patient to another and from one side of the body to the other. Obtaining a blood sample from some people may be more difficult than from others. Risks associated with having blood drawn are slight but may include:

- Excessive bleeding
- Fainting or feeling light-headed
- Hematoma (blood accumulating under the skin)
- Infection (a slight risk any time the skin is broken)

All research nursing staff will be highly trained and experienced in venipuncture thereby minimizing risk.

### **8.7.3 Test results**

False positives and false negatives are explained as follows:

No medical test is completely accurate. This blood test is expected to pick up about 40 in 100 cases of lung cancer and detect the cancer at an early stage. However this means it doesn't pick up all cases of lung cancer. So even if your test is negative, or if you are in the non-test group, it is important that you see your GP if you are unwell in any way that could be due to lung cancer. This includes persistent cough, coughing up blood, shortness of breath, weight loss or loss of appetite.

As no medical test is completely accurate, the blood test will be positive in a small number of people who do not have early lung cancer. This will happen to about 11 out of every 100 people who have a positive test result. These people will be offered chest X-rays and lung scans to see if they have lung cancer. People with a negative blood test will not get any X-rays or scans.

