a wide range of solid tumours, including lung cancer. The serum proteome provides an attractive source of potential biomarkers and because serum collection is minimally invasive it can be repeatedly surveyed for cancer biomarkers. AABs have been detected months to years before clinical diagnosis of breast and lung cancers, supporting the hypothesis that AABs could be incorporated into an early detection assay. Subsequent research studies have confirmed AABs to TAAs in patients with early stage lung cancer. AABs have been reported in lung cancer subjects up to 5 years before clinical diagnosis even where annual screening spiral CTs were being performed.

A serum assay has been developed and validated called Early Cancer Detection Test-Lung (EarlyCDT-Lung) that can detect 40% of lung cancers with a specificity of 90% by measuring autoantibodies to a panel of cancer antigens (p53, NY-ESO-1, CAGE, GBU4-5, Annexin1, & SOX2). Further confirmation of this sensitivity and specificity of the test for lung cancer using four new, independent sample sets has recently been published. A study of patient demographics showed no difference in autoantibodies based on age, gender and ethnicity. This autoantibody technology is different from CT scanning which in a prevalence screening test has a sensitivity of 67% for lung cancers developing over the following 12 months but with a low specificity of only around 49%. Indeed a prevalence CT screen will detect approximately 36% of the lung cancers which will develop in the next three years. If the EarlyCDT-Lung test has a three year 'look forward', as clinical data suggests, then the test will detect 40% of lung cancers which develop over this three year time period but with seven times fewer false positives than CT scanning. Two new autoantibodies (AABs) have recently been added to the panel (and one removed) and the test now measures seven; p53, NY-ESO-1, CAGE, GBU4-5, HuD, MAGE A4 & SOX2 and identifies 41% of lung cancers with an increased specificity of 93% (Chapman et al; 2012). The 7-AABs panel will be utilised in this study and all

statistical calculations are based on the 41% sensitivity and 93% specificity of the Early CDT-Lung test.

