## **7 STATISTICS AND DATA ANALYSIS**

### **7.1 SAMPLE SIZE CALCULATION**

The rate of lung cancer is 187/100,000 per year for patients aged 50-74 in Scotland 2008 (ISD cancer statistics). Deprivation is associated with a higher risk of lung cancer. Those in the most deprived quintile are associated with an increased risk of 1.8 times compared to the middle quintile of deprivation. (ISD cancer statistics) this gives an estimated annual lung cancer rate of 336/100,000 among the practices taking part in the study. A high risk group within this population will be selected using similar entry criteria (outlined above) as the Mayo screening study which had a 2% prevalence rate of lung cancer and a further 2% incidence rate over the following 5 years (Swensson 2005). The baseline rate of late stage presentation for the particular high risk population envisaged in this study is uncertain, as is the size of the reduction in late stage presentation likely to be achieved through use of EarlyCDT-Lung. Using an estimated late stage presentation rate of 1,200/100,000 per year in the control group i.e. 2.4% over the two-year follow-up period, we require 85% power at 5% significance (two-sided) to detect an estimated reduction of 35% in presentation rate in the test group i.e. as low as 780/100,000 per year or 1.56% over the two-year follow-up period. This corresponds to an estimated event rate over the

two years of follow-up of 120 events in the control group and 78 events in the test group and implies a required sample size of  $n=5,000$  per group i.e. 10,000 altogether.

The anticipated 35% reduction in event rate between the control group and the test group is justified by current estimates of the capability of the EarlyCDT-Lung test to identify cases (41% sensitivity, 93% specificity) together with current estimates of the specificity of CT scanning (67%).

The sample size calculations are based upon standard methods for time to event data using the `cpower` function in R and `stpower` exponential procedure in Stata and assuming exponential survival. They were also confirmed using standard approaches for detecting a change in binomial probabilities, and confirmed using approaches to detect a change in Poisson rates (with essentially identical results as loss to follow up is expected to be low).

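### Section 8.7.3 says about 11 of every 100 positive tests are false; the protocol's own figures give about 73 to 89 of every 100

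*Protocol*

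**What the plan says.** Section 8.7.3 sets out, in words addressed to the participant, what false negatives and false positives are. On false positives it first says that "the blood test will be positive in a small number of people who do not have early lung cancer". The next sentence gives the size: "This will happen to about 11 out of every 100 people who have a positive test result". The denominator is explicit: people with a positive result.

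The figures that bear on this stand elsewhere in the Protocol:

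- **Test accuracy, section 1.1.** The seven-marker panel used in the trial "identifies 41% of lung cancers with an increased specificity of 93" per cent, and all "statistical calculations are based on the 41% sensitivity and 93% specificity of the Early CDT-Lung test". An earlier panel is described as one "that can detect 40% of lung cancers with a specificity of 90" per cent.
- **Disease frequency, section 7.1.** A screening study with similar entry criteria is cited, "which had a 2% prevalence rate of lung cancer and a further 2% incidence rate over the following 5 years". The control-arm late-stage rate is set at 2.4% over two years, and the baseline rate for this population is called uncertain.
- **Expected positives, section 4.7** (repeated in the Summary and section 8.7.4). Between 400 and 450 people in the intervention arm are expected to test positive. Section 7.1 puts 5,000 in each arm.

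Section 8.7.3 also says the test is "expected to pick up about 40 in 100 cases of lung cancer and detect the cancer at an early stage".

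**The concern.** The share of positive results that are false depends on sensitivity, specificity and prevalence. When a disease affects a few per cent of those tested, a specificity of 93% makes false positives outnumber true ones by a wide margin. A false share of 11% is the pattern expected when more than half of those tested have the disease, which is not this population.

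The passage is the protocol's account of what a positive result means, and it is worded for participants. A test-positive person who relied on it would put the chance of cancer near 89%, whereas the protocol's figures put it at roughly 11% to 27%. The error runs in the direction that overstates the meaning of a positive test.

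**Working it through.** **Inputs.** Sensitivity 0.41 and specificity 0.93 (section 1.1); 5,000 tested (section 7.1); 400 to 450 positives (section 4.7). Values of prevalence *p* are taken or derived from sections 1.1, 7.1 and 4.7.

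**Formulas.** True positives = 5,000 × 0.41 × *p*. False positives = 5,000 × 0.07 × (1 − *p*). False share = false positives ÷ all positives.

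**Step 1: can the stated 11 per 100 be reproduced?** Set false : true = 11 : 89.

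*p*/(1 − *p*) = (89/11) × (0.07/0.41) = 1.381, so *p* = 58%.

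With the earlier panel (40%, 90%): (89/11) × (0.10/0.40) = 2.023, so *p* = 67%. Nothing in the Protocol comes near either value, so the figure is not reproduced.

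**Step 2: what prevalence do the expected positives imply?** Positives ÷ 5,000 = 0.41*p* + 0.07(1 − *p*) = 0.07 + 0.34*p*.

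- 400 positives: (0.08 − 0.07)/0.34 = 2.94%.
- 450 positives: (0.09 − 0.07)/0.34 = 5.88%.

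**Step 3: the false share across the supportable range.**

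| Prevalence and its source | Positives | True | False | False per 100 positives |
|---|---|---|---|---|
| 2%: screening study cited in 7.1 | 384 | 41 | 343 | 89.3 |
| 2.4%: two-year late-stage rate alone, 7.1 | 390.8 | 49.2 | 341.6 | 87.4 |
| 2.82%: 2.4% ÷ 0.85, taking the 85% advanced at diagnosis in 1.1 | 398.0 | 57.9 | 340.1 | 85.5 |
| 2.94%: implied by 400 positives | 400 | 60.3 | 339.7 | 84.9 |
| 4%: 2% prevalence plus 2% five-year incidence, 7.1 | 418 | 82 | 336 | 80.4 |
| 5.88%: implied by 450 positives | 450 | 120.6 | 329.4 | 73.2 |

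The earlier panel does not help: at 2% to 4% prevalence it gives 92.5 to 85.7 false per 100 positives.

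**Step 4: a check without Bayes' rule.** If only 11% of 400 to 450 positives were false, 44 to 50 would be false and 356 to 400 would be true cancers. Section 7.1 expects 120 late-stage cancers in the whole 5,000-person control arm over two years, or 120/0.85 = 141 of all stages. A test said to find 41% of cancers would be finding more than twice the total expected. Also, 44 to 50 false positives among some 4,860 cancer-free people means a specificity of about 99%, not 93%.

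**Step 5: where might the 11 come from?**

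- *Predictive value.* At 2% prevalence, 41/384 = 10.7 true per 100 positives. With the earlier panel at 3% prevalence, 60/545 = 11.0.
- *Share of everyone tested who is positive.* With the earlier panel this is 530/5,000 = 10.6% at 2% prevalence and 560/5,000 = 11.2% at 4%.

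**The case against.** Nobody can defend 11% as the false share among positives. The fair objections are to how much more is built on it, and several stronger readings are tempting.

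**That the predictive value was swapped for its complement.** A reader might infer this from the match at 10.7%. It is likely but not shown. The second route in step 5 gives nearly the same number through a wrong denominator, and the sentence just before speaks of a small number of people, which fits a share of all those tested. The 40-in-100 detection figure in section 8.7.3 could come from the earlier panel, or be 41% rounded.

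**That the correct figure is 85 to 89.** Accuracy alone does not fix it; a prevalence of about 2% to 3% is also needed. Section 7.1 reports the 2% as another study's result, not as this trial's planning value. The 89 rests on 384 positives, fewer than the 400 to 450 expected, and that expected count gives 85 down to 73. The wider range has to be kept.

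**That participants have been misinformed, and that the distress scores in secondary outcome 5 or the uptake of imaging are distorted.** The information sheets are not at hand, so it is unknown whether the sentence appears there. Test-positive participants are offered a visit or call to interpret the result and receive a second information sheet (sections 2.2, 2.4 and 4.1). Section 8.7.3 itself says imaging is offered to find out whether they have cancer. Any effect on those outcomes is conjecture, and for imaging even its direction is unclear.

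**That the phrase on early-stage detection is a second contradiction.** Section 1.1 says positivity does not differ between early and late disease, but also that the test does find early disease. The lay phrase is loose rather than plainly false.

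All four objections limit the point. None rescues the sentence.

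**Conclusion.** The sentence is wrong as written. On the protocol's own figures, about 73 to 89 of every 100 positive results are false, against the stated 11: an understatement of 73.2/11 = 6.7-fold to 89.3/11 = 8.1-fold.

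The range assumes 41% sensitivity, 93% specificity, 5,000 tested and a prevalence between 2% and 5.88%. Most of its width comes from the protocol's own inputs: the cited 2% implies 384 positives, while the top of the expected count implies nearly three times that prevalence. The conclusion does not depend on where in the range one stands. Reading the reference to early lung cancer literally, so that positives with late disease also count as false, would only raise the false share.

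How the 11 arose cannot be settled from the document, and neither can whether participants were shown it. The sample size, primary endpoint and planned analyses do not use the figure and are unaffected.

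**What to change.** Replace the sentence in section 8.7.3 with one saying that most people with a positive result, roughly 3 in 4 to 9 in 10, will not have lung cancer. If a single figure is preferred, derive it from one stated prevalence and one stated time horizon that also reproduce the number of positives expected in section 4.7. Point prevalence and two-year incidence should not be mixed in the same figure.

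Check the participant information sheets for the same sentence. If it is there, correct and reissue them, with notification to the ethics committee.

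As a minor point, reword the phrase on detection at an early stage so that it matches section 1.1: the test can be positive at any stage.

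The cost is a wording amendment, plus reissue of the sheets if they carry the sentence. No change to design, sample size or analysis follows.

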### **8.7.4 Radiography**

Risks relating to chest X-ray and CT scan are explained as follows:

Chest X-rays and lung scans use radiation. People can develop cancer because of this radiation, but this is very rare. The amount of radiation you get from a chest X-ray is very small. About 1 million people would need to have a chest X-ray for one extra person to develop cancer because of the chest X-ray. A CT lung scan gives about 600 times as much radiation as a chest X-ray. 1500 people would need to have a CT lung scan for one extra person to develop cancer because of the scan. These risks are very small compared to the one in four chance we each have of developing cancer in our lifetime. Only about 400-450 people in this study are expected to have a positive blood test and will, therefore, need chest X-rays and scans. The chances of radiation affecting anyone in this study in this way are therefore very small.

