**Visit 2 @ GP/CRF (~30 -45 mins)**

- CXR/Study CT arranged
- Summary information given/posted to Participant (PIS 2)
- Participation & Results Letter sent to GP

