#### 6 MONTHLY STUDY CT SCANS

- Participant given appointments to attend for Study CT scans every 6 months for 2 years. Research team call 2-4 days before CT appt.

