### CXR & STUDY CT SCAN @ LOCAL HOSPITAL

- Participant attends for CXR
  - If CXR negative participant attends for CT scan
  - If CXR positive or suspicious participant informed to attend for NHS CT scan and seen by PI (Respiratory Physician) if required
- (if NHS pathway negative, participant remains in study pathway)*

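### Section 8.7.4 calls the study-wide chance of a radiation-induced cancer very small, but its own figures put it at about 23–26% with one CT each; it also gives only the single-scan risk when up to five CTs are scheduled

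*Protocol*

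**What the plan says.** Section 8.7.4 is worded as an explanation to participants. It puts the chest X-ray risk at one extra cancer per million people and gives the CT dose as about 600 times that of an X-ray. For CT it states: "1500 people would need to have a CT lung scan for one extra person to develop cancer because of the scan". It then compares the individual's risk with background: "These risks are very small compared to the one in four chance we each have of developing cancer in our lifetime". Next comes the number exposed: "Only about 400-450 people in this study are expected to have a positive blood test and will, therefore, need chest X-rays and scans". From this it concludes: "The chances of radiation affecting anyone in this study in this way are therefore very small".

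The imaging pathway is set out elsewhere:

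- **Section 2.2 (flowchart), first CT.** Both X-ray outcomes lead to a CT: "If CXR negative participant attends for CT scan" and "If CXR positive or suspicious participant informed to attend for NHS CT scan".
- **Section 2.2 (flowchart), repeats.** "Participant given appointments to attend for Study CT scans every 6 months for 2 years".
- **Section 2.4, Table 1.** CT is marked at 0, 6, 12, 18 and 24 months. Remaining study scans are cancelled if the participant moves into NHS care.
- **Section 4.7.** Six-monthly repeat CTs over 24 months are offered after a negative initial CT.

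Section 8.7.4 uses the plural for scans but gives neither their number nor a cumulative risk.

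**The concern.** The closing sentence of section 8.7.4 argues from how few people are scanned to a statement about the whole study. Several hundred exposures at 1 in 1,500 each do not make a negligible total, so the conclusion looked inconsistent with the two figures printed just before it.

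The second question is whether a per-scan figure describes what a test-positive participant takes on when the schedule allows five scans.

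At stake is the accuracy of a harm statement addressed to participants, most of whom will not have lung cancer. The protocol recognises this harm itself: section 1.3 counts repeated radiation exposure in people without cancer among the drawbacks of CT screening.

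**Working it through.** The protocol attaches no number to its conclusion, so there is no figure to reproduce. The check is whether its inputs support the words.

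**Inputs**

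- Risk per CT: p = 1/1,500 (section 8.7.4).
- People imaged: n = 400 to 450 (section 8.7.4).
- CTs per person: k = 1 as the base case (section 2.2 directs every attending test-positive participant to a CT); k = 5 as the ceiling (Table 1).
- Trial size: 10,000 (section 2.1).

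**Formulas**

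- Expected extra cancers = n × k × p.
- Chance of at least one = 1 − (1 − p)^(n × k).

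**One CT each**

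- n = 400: expected 400/1,500 = 0.267; chance 1 − (1,499/1,500)^400 = 0.234.
- n = 450: expected 450/1,500 = 0.300; chance 1 − (1,499/1,500)^450 = 0.259.

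**Sensitivity of the one-CT result**

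- Per-CT risk taken from the 600-fold dose ratio: 600 per million, or 1 in 1,667. The chance is 21.3% to 23.7%.
- Adding one chest X-ray each at 1 in a million raises the chance by about 0.03 percentage points.
- If only 80% attend the one CT (my assumption): 320/1,500 = 0.213 and 360/1,500 = 0.240 expected; chance 19.2% and 21.3%.
- For scale, the number of CTs that gives a 5% chance is −ln(0.95) × 1,500 = 76.9, so about 77 scans in the whole study. The 5% line is mine; the protocol sets none.

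**More than one CT each (n = 400 to n = 450)**

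| CTs per person | Expected extra cancers | Chance of at least one |
|---|---|---|
| 1 | 0.27–0.30 | 23–26% |
| 2 | 0.53–0.60 | 41–45% |
| 3 | 0.80–0.90 | 55–59% |
| 4 | 1.07–1.20 | 66–70% |
| 5 (ceiling) | 1.33–1.50 | 74–78% |

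The last row is a ceiling. Repeats follow a negative CT, entry into NHS care cancels later study scans, and non-attendance and deaths reduce the number. The protocol does not give an expected average number of scans.

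**Risk to one participant who completes the schedule**

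- 5 × 1/1,500 = 1/300 = 0.33%, against 1/1,500 = 0.07% for one scan.
- Against the lifetime risk of one in four: 0.33%/25% = 1.3%.

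**Risk averaged over all participants (the alternative reading)**

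- One CT each: 0.267/10,000 = 1 in 37,500; 0.300/10,000 = 1 in 33,333.
- Five each: 1.333/10,000 = 1 in 7,500; 1.500/10,000 = 1 in 6,667.

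**The case against.** The strongest reply is that the sentence is addressed to a reader who does not yet know their allocation or test result. For that reader the relevant risk is the chance of being scanned times the chance of harm if scanned. The number exposed is a proper input to that product, so its appearance in the argument does not prove that a study-wide claim was meant. On this reading the risk is very small, even at the five-scan ceiling. No printed number is wrong, and the protocol sets no threshold for its verbal conclusion.

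Part of this stands: the averaged reading exists and is valid on its own terms. But the sentence speaks of anyone in the study being affected, and that is most naturally the chance of at least one case. The individual comparison with lifetime risk has already been made two sentences earlier. A figure averaged over more than 9,500 people who get no study imaging is also of little use to a test-positive participant, whose own risk does not depend on how few others are scanned. Nor is an outside threshold needed: the section uses one in four as its large benchmark, and the study-wide chance comes to about one in four.

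On the repeat scans, the reply is that the section labels its figure as per scan, that the schedule is open elsewhere in the protocol, and that test-positive participants receive a second information sheet (PIS 2) when imaging is arranged. All of this is correct. PIS 2 is not available here and may give the cumulative risk, so the omission is established for section 8.7.4 only.

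**Conclusion.** The point holds, at minor severity. As written, the study-wide sentence is wrong on its literal reading and at best misleading. Its own inputs give 0.27–0.30 expected extra cancers and a 23–26% chance of at least one with a single CT each. The result stays at roughly 19–26% under the alternative per-scan risk and under 80% attendance at that one CT, and repeat scans raise it.

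The section also leaves out the cumulative risk of the schedule, about 1 in 300 for a participant who completes five CTs, five times the only CT figure given. The message that individual risk is small beside lifetime risk survives.

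This rests on the protocol's own 1 in 1,500, on every test-positive participant having one CT in the base case, and, for one person's repeat scans, on risk adding linearly. The 74–78% at five scans each is a ceiling, and the main conclusion does not depend on it. Nothing in the design, the scan schedule or the statistical analysis is affected.

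**What to change.** In section 8.7.4:

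1. Delete the closing sentence, or restrict it to the risk of the individual participant.
2. State that participants with a positive test may have up to five CTs over 24 months, with a cumulative risk of up to about 1 in 300, set against the one-in-four lifetime risk.
3. Check that the participant information sheets, including PIS 2, say the same.

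The cost is a wording change and a check of the sheets, with no change to design, schedule or analysis.
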